#### Secondary Study Parameter(s)

The main secondary outcomes are child preprocedural anxiety at T2 and parental anxiety both before and during the procedure.

For the child’s preprocedural anxiety, we will employ an identical analysis as for the primary end point. For parental anxiety, a repeated measures ANCOVA will be conducted with parental anxiety at T2 and T3 as within variable and group (VR vs CAU) as between variables. The analysis will be corrected for age, sex, baseline anxiety, and CBCL scores as well as type of MRI.

To identify medical or psychosocial moderators for treatment response to VR, we will perform exploratory linear regression analyses with child anxiety at T2 and T3. Predictor variables that will be examined are SES, age, sex, type of MRI, preprocedural child and preprocedural parental anxiety, and child emotional and behavioral problems. The user experience of children in the VR condition will be examined with descriptive analyses.

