### Sample Size

To conduct analysis of covariance (ANCOVA) on the level of periprocedural anxiety at time point (T) 3 (primary outcome) with a Cohen *d* of 0.5, an α of .05 (2-tailed), and a power of .80, a sample size of 128 patients is needed (64 patients per group). Based on earlier studies, we anticipate finding a medium effect size [16].

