### Patient Recruitment and Procedure

For the prospective recruitment of patients, in concert with the radiologist, the planned MRIs will be scanned a month ahead for eligible patients. They will be informed about the study by mail or phone. If needed, they will be reminded by phone in the following weeks. Besides the reminder, this will help to overcome doubts, because the staff can answer questions or motivate the patients to participate.

All participants will receive an invitation, information folders, and an informed consent form. Participation is not obligatory, and all data will be anonymized. Parents of all the patients will be asked to sign informed consent. Children aged 12-14 years will also be asked to provide informed assent themselves. Patients aged younger than 12 years will give their verbal permission.

After receiving signed informed consent, the participants will be stratified by the type of MRI scan (head or body scan). Then, they will be randomly assigned to the VR group (n=64) or the CAU group (n=64).

The children assigned to the VR group will receive Google cardboard–like VR glasses and instructions on how to download the VR app on their phone and use the VR intervention at home. They will receive a log-in code to use the smartphone VR app. Adherence will be promoted by giving the participants detailed information about the purpose of the study and how to use the VR preparation app and explaining how they can get help from the contact support staff if there are difficulties with the app or VR glasses.

The allocation sequence was executed by a researcher who is not involved in the assessment phase. The psychologist who assesses the child’s anxiety state is blinded to the group assignment. This way, blinding for the treatment allocation will be guaranteed. Parents and children in both groups will be asked not to discuss their treatment allocation with the nurse, radiologist, or research psychologist.

Questionnaires will be assessed at the following time points: (1) T1, the weeks before the MRI scan (at home); (2) T2, the day of the MRI scan, before the procedure will start (in the waiting room); and (3) T3, right after the MRI scan (in the waiting room). The T3 questionnaires will retrospectively assess the child’s experience during the MRI scan. In this way, we can measure the anxiety during the MRI scan without the interruption of the procedure.

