#### Child Anxiety

The anxiety level of participants is measured before and after the MRI scan (T2 and T3) with the STAI-C, a questionnaire where parents and children evaluate statements on a scale from 0 (not at all) to 4 (completely true). The STAI-C is a widely used and validated self-report instrument for measuring state and trait anxiety [24]. The STAI-C has a good-to-excellent interobserver and intraobserver reliability and was validated in Dutch [25]. The VAS will be used to assess the child’s anxiety level by the child himself, the parents, and the medical staff. The VAS shows 6 faces in order from not scared at all (most left face) to extremely scared (most right face; see Figure 3) [26]. The participants select the expression that fits their feeling before and after the MRI scan (T2 and T3). Because of the nonverbal character and the simplicity, this instrument offers a quick and reliable assessment that can be used in different settings [27,28]. The VAS is a widely used and studied instrument, has been shown to have a good reliability and validity, and is validated in Dutch [29]. The medical staff who accompanied the child were instructed to observe the anxiety of the child before the procedure in the MRI room and during the MRI scan (T2 and T3) by using the VAS [30].

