#### Parental Anxiety

Parents/guardians rate their own feelings of anxiety with the STAI at T2 and T3. This self-report instrument contains 2 separate scales for trait and anxiety, combined into 40 items that the respondent rates as not at all (0), somewhat (1), moderately (2), or very much (3). Earlier studies identified the STAI as a validated and reliable instrument to measure the anxiety state of the parents, and it is validated in Dutch [24,32].

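### The moderator list for VR response includes preprocedural child and parental anxiety, which are measured after home VR use and, for the child, overlap the T2 outcome

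*Protocol article*

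**What the plan says.** Secondary Study Parameter(s) states the aim and the method in one sentence: "To identify medical or psychosocial moderators for treatment response to VR, we will perform exploratory linear regression analyses with child anxiety at T2 and T3". The candidates follow: "Predictor variables that will be examined are SES, age, sex, type of MRI, preprocedural child and preprocedural parental anxiety", together with child emotional and behavioral problems. Neither the randomised group nor any product of group with a predictor is mentioned.

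The same section fixes what preprocedural means for the child: "The main secondary outcomes are child preprocedural anxiety at T2 and parental anxiety both before and during the procedure". The instrument sections agree on timing. For the child, "The anxiety level of participants is measured before and after the MRI scan (T2 and T3) with the STAI-C", and the faces scale is given at the same two visits. For the parent, "Parents/guardians rate their own feelings of anxiety with the STAI at T2 and T3". Patient Recruitment and Procedure places T2 in the waiting room on the day of the scan, after the period in which the VR group has the app at home. The last paragraph of the Introduction hypothesises that VR reduces both preprocedural child anxiety and parental anxiety more than care as usual.

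**The concern.** A moderator is a characteristic across which the VR-versus-CAU difference varies. To be read that way in a randomised comparison, it must not itself be changed by the allocation. Two of the listed candidates fail that condition on the protocol's own hypothesis. Children with the same T2 anxiety in the two arms are no longer comparable by randomisation, because in one arm that level was reached with VR and in the other without it. A VR effect that seems to depend on T2 anxiety could simply reflect how VR acted on T2 anxiety.

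The T2 regression has a second problem. Its outcome is child anxiety at T2, and the shared list offers preprocedural child anxiety as a predictor.

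Third, if the listed predictors were entered only as main effects, their coefficients would say which children are more anxious, not which children gain from VR. At stake is what the exploratory analysis may conclude about who benefits; the test of VR against CAU is not at stake.

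**Working it through.** **1. Timing, set side by side**

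| Candidate | When measured | Could VR change it? |
|---|---|---|
| SES, age, sex, type of MRI | fixed at entry | no |
| Behavioral and emotional problems (CBCL) | T1, about the last 6 months | not plausibly |
| Preprocedural child anxiety | T2 | yes, hypothesised in the Introduction |
| Preprocedural parental anxiety | T2 | yes, hypothesised in the Introduction |

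**2. T2 child anxiety in the T2 model.** If instrument and informant are the same on both sides, the regression returns a coefficient of 1 for that predictor, R-squared of 1, and 0 for every other term; a simulated dataset confirmed this. If they differ (for example VAS against STAI-C, or child against parent rating), the fit is not exact, but a second reading of the same state at the same visit absorbs much of what the other predictors could explain. How much depends on correlations that the article does not give.

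**3. T2 anxiety in the T3 model.** Illustration with assumed values: VR effect on T2 of -0.5, slope of T3 on T2 of 0.6, direct VR effect on T3 of -0.2. The total effect is -0.2 + 0.6 × (-0.5) = -0.50. Simulation (2,000 runs, N = 128) gave -0.50 without T2 in the model and -0.20 with it. Part of the VR effect has passed into the T2 term, which is how a mediator behaves.

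**4. Main effect against interaction.** Simulation of 4,000 trials, 64 per arm, residual SD 1, VR effect -0.5, assumed 50:50 binary covariate. Share of trials with p < .05 for the covariate term:

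| Truth | Group + covariate | VR arm only | Interaction |
|---|---|---|---|
| Prognostic 0.5 SD, no moderation | 80% | 50% | 4.9% |
| Interaction 1.0 SD, average main effect zero | 4.7% | 51% | 80% |

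A model without the interaction flags the variable that does not moderate and misses the one that does.

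**5. What the interaction test can deliver.** The plan's own figure comes first: "with a Cohen *d* of 0.5, an α of .05 (2-tailed), and a power of .80, a sample size of 128 patients is needed". The normal approximation gives 2 × (1.960 + 0.842)² / 0.5² = 62.8, so 63 per arm. The exact t test gives 63.77, so 64 per arm and 128 in total, with power 0.801. The stated size is reproduced.

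For a 50:50 moderator there are four cells of 128 / 4 = 32. The interaction is a difference of two differences, so SE = sqrt(4 / 32) = 0.354 SD.

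- Detectable at 80% power: 2.80 × 0.354 = 0.99 SD.
- Power for a 0.5 SD interaction: 0.5 / 0.354 = 1.414, and Φ(1.414 - 1.960) = 0.29.
- N for 80% power at 0.5 SD: ((1.960 + 0.842) × 4 / 0.5)² = 502.3, so about 503 children.

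**The case against.** The strongest reply concerns the interaction term. A reader might infer that the protocol commits to main effects only and so cannot identify moderators at all. The text does not support that. It states a moderator aim, names a model family and gives a list of candidates; it does not write out a model equation or say that main effects will be read as moderation. Even the randomised group goes unlisted, which suggests condensation. The exact terms of an exploratory regression are commonly left to a fuller plan. This part therefore stands only as a request to state the term. The simulation shows why the term matters, not what the trial will do.

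On the T2 overlap, the list may be pooled for two outcomes, with preprocedural anxiety meant only for T3. An outcome regressed on itself would also be noticed at once. A reader might infer an R-squared of 1 by construction, but that needs the same instrument and informant on both sides, and the section does not say which are used. The practical risk is small. The wording still assigns the predictor to both outcomes and should be corrected.

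The Primary Study Parameter(s) section names baseline anxiety as a covariate, and Figure 2, not shown here, may contain an earlier anxiety measure. The listed candidate is nevertheless called preprocedural, which the same section ties to T2 for the child. The parental questionnaire has a trait scale that VR would be less likely to change, but the list does not restrict itself to it.

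None of this answers the main point: T2 follows the intervention, and adding an interaction term would not cure that.

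**Conclusion.** The point holds for two of the listed candidates. Preprocedural child and parental anxiety are post-intervention variables that VR is expected to lower, so in the T3 model they are candidate mediators, not moderators. In the T2 model, preprocedural child anxiety also overlaps the outcome. SES, age, sex, type of MRI and T1 behavioral problems remain legitimate candidates, so the analysis as a whole is not invalid. The absent group-by-predictor term is a matter to make explicit, not an established error.

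Severity is low to moderate: the analyses are labelled exploratory, and neither the primary comparison nor the main secondary comparisons depend on them. The 0.99 SD and 29% figures rest on an assumed 50:50 moderator, SD 1, all 128 children analysed and no covariate adjustment. They describe the limits of the corrected analysis, not the size of an error in the protocol.

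**What to change.** - Limit candidate moderators to variables fixed before randomisation: SES, age, sex, type of MRI and T1 CBCL scores. State that the CBCL is completed before allocation is known; the article places it at T1 but does not give the order.
- Fit each model in both arms with group, predictor and group-by-predictor interaction. Report the interaction estimate with its 95% CI, labelled exploratory.
- Remove T2 child and parental anxiety from the moderator list, or present them under a separate heading as an exploratory mediation question for T3. Do not use T2 child anxiety as a predictor in the T2 model.
- Name the instrument and informant for each outcome.
- If interactions are not intended, retitle the analysis as one of predictors of anxiety.

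The cost is a few sentences and a few lines of code, with no new data. The downside is wide intervals: under the assumptions above, only interactions near 1 SD would be found reliably.

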## Results

The final version of the VR app has been approved. The recruitment of participants started in May 2021 and is currently ongoing and expected to be completed in December 2022. Data will be analyzed, and scientific papers will be submitted for publication in 2023.

## Discussion

### Expected Findings

Children often experience an MRI scan as an anxiety-provoking situation, and therefore, it is urgently needed that effective psychological preparations that are easy to use and cost-effective are developed and offered. VR has the potential to become a promising tool in the psychological preparation of pediatric patients for MRI. VR exposure has already been shown to be effective as a treatment for specific phobias in children. However, despite the fast-growing field of VR in medical care, there has been little research into the effectiveness of VR as preparation for an MRI scan in a clinical setting. Since VR is a promising tool for improvement in health outcomes, high-quality studies investigating innovative VR interventions are needed. Here, we describe the development of a smartphone-based VR intervention to prepare children for MRI scanning as well as an RCT to test its efficacy.

### Strengths and Limitations

This study design has both strengths and limitations. A strength of this study is the RCT design and the multiple informant assessment of anxiety in children before and during the MRI scan. Most of the current preparation materials for children undergoing an MRI scan involve verbal explanation. The use of VR combines verbal explanation with visual information that can be beneficial for younger children or children who do not speak or understand the language. Additionally, the use of mobile phone–based VR creates the possibility to prepare children in their own time, at their own pace, and in the comfort of their own home. It also alleviates the personnel and space demands imposed by mock-scanner preparation. Due to the use of a smartphone-based VR experience that can be used at home, we can reduce the costs associated with using a tethered VR experience. The app presents a typical MRI room and thus can be used in any hospital without adjustments. Moreover, the app is designed to be easily localized to other languages. Furthermore, due to the use of 3D models instead of 360-degree video recordings, adjustments and adding or subtracting certain elements can be easily and cheaply done.

A limitation is that although we ask participants in the user experience questionnaire how often and for how long they have used the VR preparation app, we do not have more accurate measures of VR use. In addition, as the VR intervention is designed to be used at home in an environment that is comfortable for a child, we do not have information if the children used the VR MRI app with enough attention. The smartphone used by each child varies greatly in screen quality, size, and processing power. These differences might influence the VR experience, its image quality, and ultimately, the immersivity of the VR. Another limitation is that only children who do not need general anesthesia during the MRI scan are included, thereby potentially excluding the most highly anxious children. This may limit the generalizability of this study to children with less severe levels of anxiety. If this study shows that the VR MRI preparation app is efficacious, it would be important to study whether VR preparation can also reduce the need for anesthesia.

### Conclusion

Most children experience anxiety before and during an MRI scan. To reduce this and reduce the need of anesthesia, there is a need to develop a more effective preparation method. VR offers a child-friendly and realistic environment where children can experience the procedure, without the use of real machines or medical staff. To examine the effect of this VR intervention, an RCT will be performed. If VR exposure is proven to be effective for preparation for an MRI scan, this easy-to-use tool can be implemented into standard medical care. We would like to emphasize though that even with the use of modern technology, education provided by health care professionals for both pediatric patients and their parents is still necessary, especially for older children.

## Appendix

Multimedia Appendix 1 Images of the 3D environment in which the VR-experience takes place.

## Abbreviations

ANCOVA: analysis of covariance
Amsterdam UMC: Amsterdam University Medical Centers
CAU: care as usual
CBCL: Child Behavioral Checklist
Erasmus MC: Erasmus University Medical Center
MRI: magnetic resonance imaging
RCT: randomized controlled trial
SES: socioeconomic status
STAI: State-Trait Anxiety Inventory
STAI-C: State-Trait Anxiety Inventory for Children
T: time point
VAS: Visual Analog Scale
VR: virtual reality
